#### Phase 1 (T0)

Following the presentation of the study and the signing of the informed consent, participants will be asked to fill out the socio-demographic data, the clinical history of illness, any ongoing psychological support course, and a series of questionnaires aimed to explore some psychological aspects. Specifically, the following questionnaire will be administered:

- *The multidimensional assessment of interoceptive awareness* (MAIA; Mehling et al., 2012): The MAIA is a self-report questionnaire that assesses eight dimensions related to interoceptive aspects of body awareness. The scale has a total of 32 items on a 6-point Likert scale, from 0 (never) to 5 (always), and covers eight “distinct but related” dimensions of interoception: *awareness of bodily sensations* (e.g., “I can tell where I feel good in my body”), the *tendency to ignore uncomfortable bodily sensations* (e.g., “I distract myself when I feel uncomfortable or fearful sensations”), the *ability to have emotional reactions following negative sensations* (e.g., “I worry if I feel pain or uncomfortable sensations”), the *ability to adjust attention regarding multiple sensations* (e.g., “I can focus sensations on my body, even when there are many distractions around me”), the *ability to be aware of the relationship between body states and affective states* (e.g., “I can feel changes in my body when I am happy”), the *ability to pay attention to body states to regulate psychological* distress (e.g., “I can use my breath to help me stay calm and relaxed”), the *ability to feel one's bodily sensations to make decisions* (e.g., “I listen to my body to help me choose what to do”), and *the experience of one's body as safe and trustworthy* (e.g., “I feel that my body is a safe place”). Some subscales measure direct experience with the body, and others are associated with the assessment of cognitive processes, such as self-regulation (Mehling et al., 2012).- *Cancer Worry Scale* (CWS; Custers et al., 2014; Chirico et al., 2022): The CWS is a self-report questionnaire designed to measure concerns with respect to the recurrence of cancer disease. The questionnaire has eight items on a 4-point Likert scale (from “never” to “almost always”). The higher the score, the greater the concern related to the fear of cancer recurrence.- *State-Trait Anxiety Inventory* (STAI-Y1; Spielberger, 1983; Spielberger et al., 1983): The STAI is a self-report questionnaire aimed at assessing anxiety as a transient emotional response involving negative feelings related to, for example, nervousness, worry, and tension. As a revised version of the original STAI-X, it presents 20 items on a 4-point Likert scale (from “nothing” to “very much”) with a range of total scores between 20 and 80 (high anxiety).- *Self-Assessment Manikin* (SAM; Bradley and Lang, 1994): The SAM is a non-verbal self-report measure in which nine figures (manikins) are shown in groups of three to measure the emotional response (positive to negative) and the relative level of activation (high to low) and control (low to high) identified by the subject as central to a specific stimulus.- *Checking Behaviors*: Some *ad hoc* questions will be administered to measure the frequency and concern of attitudes toward one's internal body sensations. Participants will have to answer some questions on a 10-point Likert scale, including the following: (a) *In the past 7 days, how often have you checked your breasts for lumps?* (b) *In the past 7 days, have you felt anxious?* and (c) *How many times have you told your family members about your fears related to the disease in the past 7 days?*

The duration of T0 will be about 20 min.

#### Phase 2 (T1)

Subsequently, participants will be randomly divided into the experimental and control groups. Participants in the experimental group will be asked to sit on a chair and place their open palms on the table without crossing their legs and keeping their backs straight. Wearing 3D oculus and donning the sensor, the participants will be immersed in VR where they will see the virtual body of an avatar positioned in the same position as them. The experiment will begin with an initial warm-up phase in which participants will be allowed to stand in the virtual environment without receiving additional stimuli (2 min). In this first phase, psycho-physiological indices (heart rate and heart rate variability) will be measured using wearable sensors at the wrist so as not to interfere with the session. Next, the experimental group will observe via VR visual stimulation on different parts of the virtual body (breasts, fingers, and toes) and listen to vocal stimulation, in a consecutive and randomized manner among the group participants. Specifically, this intervention will be structured as follows: The participants will see a light on their virtual body that, starting from an iridescent red color, will fade slowly, becoming white. At the same time, an external voice will guide the participants toward a gradual decrease in sensations of discomfort and itching, in a combination of the visual stimuli. This treatment will initially be proposed for a total of 5 min, considering that 90 s is sufficient to induce body illusion. This process will be proposed in the same mode (duration equal to 5 min) for the body parts of interest of the same (breasts, fingers, and toes), with a 2-min break between stimulations. During the breaks, participants will remain immersed in VR, without additional stimulation. In contrast, participants assigned to the control group, once immersed in a VR depicting a natural environment, will hear only a guiding voice reading a script aimed at relaxation. Once the experiment is over, all participants will fill out the battery of post-intervention questionnaires, which includes the following:

- *The multidimensional assessment of interoceptive awareness* (MAIA);- *Measures regarding satisfaction related to the intervention*: participants will answer some *ad hoc* questions designed to measure their satisfaction with the intervention;- *ITC-Sense of Presence Inventory* (ITC-SOPI; Lessiter et al., 2001): The ITC-SOPI is a validated questionnaire consisting of 44 items to explore users' experience of virtual reality. Specifically, it assesses the degree to which subjects experience a “sense of presence in a virtual environment,” how distant the virtual environment is from reality, and how far the virtual environment can be considered a “place.” The items refer to the following four categories: (1) *Spatial Presence*: how physically present users perceive themselves to be in the virtual environment; (2) *Involvement*: how much users perceive the content proposed by the virtual environment; (3) *Ecological Validity*: the level of realism and naturalness of the virtual environment; and (4) *Negative Effects*: the disruptive effects on the physical plane, such as nausea and eye discomfort, that users might experience while immersed in the virtual environment.

#### Phase 3 (T2)

Lastly, a final administration of questionnaires will be conducted 1 month after the end of the intervention. Specifically, in this phase, the *Multidimensional Assessment of Interoceptive Awareness* (MAIA), the *State-Trait Anxiety Inventory* (STAI-Y1), the *Self-Assessment Manikin* (SAM), and the *Checking behaviors*, the *Cancer Worry Scale* (CWS) will be administered to participants (see Figure 1).

**Figure 1 F1:**
[figure not shown]
Study procedure.

## Data analysis and sample size estimation

An *a priori* estimation of the sample size required for the present study was calculated using G*Power 3.1.9.2 software (Faul et al., 2007) to analyze variance with repeated measure (ANOVA) with between–within interaction. The primary endpoint will be the difference between the two experimental groups (i.e., between-subject factor) in the improvement of the overall MAIA scale score at pre- (T0), post-intervention (T1), and follow-up (T2) times. To detect a weak-median effect size (i.e., partial η^2^ = 0.04), the required sample size is 40 (i.e., 20 participants in each group). The type-I error rate (α) was set at 0.05 (two-sided), and the power (1 – β) was set at 0.90. The collected data could be analyzed using a statistical analysis software, the Statistical Package for Social Science (SPSS, version 27.0).

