## Abstract

Women who received a diagnosis of breast cancer often report impairments in physical and psychological wellbeing, even some years after treatments. Individual awareness about physical changes, body image, and current sensations related to their body is important to maintain a psycho-emotional balance. Virtual reality, as an advanced human–computer interface, can be an effective tool to improve breast cancer survivors' abilities to know and manage their current sensations related to their bodies. The present study protocol proposes a virtual reality intervention aiming at promoting interoception and emotional wellbeing, fear of cancer recurrence, and body perception in breast cancer survivors, according to the three data collection times. Repeated-measure analysis of variance (ANOVA) with between–within interaction will be performed. Expected results include participants' awareness of their internal feelings, the reduction of negative emotions, and the management of symptoms related to the body, clarifying characteristics for the effective implementation of VR psychological intervention in the future.

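### The primary interaction test uses the pre-randomisation T0 MAIA score as an outcome level; adjusting for T0 instead would usually give more power at almost no cost

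*Protocol article*

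**What the plan says.** The Abstract of the protocol article names the method: "Repeated-measure analysis of variance (ANOVA) with between–within interaction will be performed". The section Data analysis and sample size estimation defines the endpoint: "The primary endpoint will be the difference between the two experimental groups (i.e., between-subject factor) in the improvement of the overall MAIA scale score", measured "at pre- (T0), post-intervention (T1), and follow-up (T2) times". The sample size rests on the same interaction: "To detect a weak-median effect size (i.e., partial η^2^ = 0.04), the required sample size is 40", that is "20 participants in each group", with alpha 0.05 and power 0.90.

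On timing, the MAIA is among the questionnaires in Phase 1 (T0). Phase 2 (T1) then opens: "Subsequently, participants will be randomly divided into the experimental and control groups". The T0 score is therefore a pre-randomisation baseline, and the planned test treats it as the first of three levels of the outcome. The article does not name T0 as a covariate.

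**The concern.** Because allocation follows T0, any difference between arms at T0 is chance. If T0 sits in the time factor, the interaction is built from changes from baseline, so the random error in T0 enters the comparison at full weight. If T0 is a covariate, it is weighted by how well it predicts the later scores, and the residual variance is smaller whenever the correlation is below 1. With 40 participants, that precision is worth having, and the T0 score is collected anyway. At stake is the chance of detecting a real effect; the false-positive rate is not in question.

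**Working it through.** **Inputs from the article.** N = 40, 20 per arm, three times (m = 3), partial η² = 0.04, alpha 0.05, target power 0.90.

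**Assumptions.** The article gives neither the correlation ρ between measurements nor the effect pattern. I take equal correlations of 0.5, 0.7 and 0.8, a 0.6-SD effect present at both T1 and T2 (sustained), and complete data.

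**Step 1. The plan's own figure.** f² = 0.04/0.96 = 0.0417, so f = 0.204. The G*Power noncentrality is λ = f²·N·m/(1−ρ), with 2 and 2(N−2) = 76 df. At the software default ρ = 0.5, λ = 0.0417 × 40 × 3/0.5 = 10.0. Power is then 0.80, and 90% power needs N = 54. N = 40 reaches 0.90 when ρ is about 0.62. Without ρ, the figure of 40 can be neither confirmed nor refuted, and the present point does not rest on it.

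**Step 2. Variance at one follow-up time.** A change score has variance 2(1−ρ) in SD² units; a T0-adjusted score has 1−ρ². The ratio is (1+ρ)/2: 0.75 at ρ = 0.5, 0.85 at 0.7 and 0.90 at 0.8.

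**Step 3. Planned interaction, sustained effect.** The group differences are (0, 0.6, 0.6), with mean 0.4. The squared deviations sum to 0.16 + 0.04 + 0.04 = 0.24. λ = (20/2) × 0.24/(1−ρ) = 2.4/(1−ρ), with 2 and 76 df.

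**Step 4. T0-adjusted joint test of T1 and T2.** The residual covariance has 1−ρ² on the diagonal and ρ−ρ² off it. For equal effects, λ = 10 × 2 × 0.36/(1+ρ−2ρ²) × 36/37, with 2 and 36 df. The factor 36/37 allows for estimating the covariate slope.

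| ρ | λ, planned | Power, planned | λ, adjusted | Power, adjusted |
|---|---|---|---|---|
| 0.5 | 4.8 | 47% | 7.0 | 62% |
| 0.7 | 8.0 | 70% | 9.7 | 77% |
| 0.8 | 12.0 | 87% | 13.5 | 89% |

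Simulation agrees: 48% against 62% at ρ = 0.5, and 68–70% against 76–78% at ρ = 0.7. Type I error of the adjusted test is about 5%.

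**Step 5. Effect at T1 only, equal correlations.** The differences (0, 0.6, 0) have mean 0.2, and the sum is again 0.04 + 0.16 + 0.04 = 0.24, so the planned power is unchanged. The adjusted test gives 49% against 47% at ρ = 0.5 and 69% against 70% at ρ = 0.7, so the two are about equal.

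**Step 6. The article's own effect size.** At ρ = 0.5, a sustained effect d gives λ = 10 × (2/3)d²/0.5 = 13.33d². Setting this to 10 gives d = 0.87. At N = 40, planned against adjusted power is 0.80 against 0.92 at ρ = 0.5, 0.90 against 0.95 at ρ = 0.62, and 0.995 against 0.997 at ρ = 0.8.

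**Step 7. A case that goes the other way.** Take correlations of 0.85 (T0–T1), 0.60 (T0–T2) and 0.60 (T1–T2), with the effect at T2 only. Simulated power is about 60% for the planned test and 52% for the adjusted test. The planned test without a sphericity correction is slightly anti-conservative in this setting, with type I error about 6%.

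**The case against.** The strongest reply is that nothing here is wrong. A group-by-time interaction is a legitimate test of a between-group difference in change, which is the endpoint the article defines, and the sample size uses the same test. Under equal correlations it holds its type I error. All of that stands, so the point concerns efficiency only.

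The gain is also conditional. It nearly disappears at ρ = 0.8 or for an effect at one time, and it reverses in Step 7. A single VR session with follow-up at one month makes a fading effect plausible. That stands too, and is why the gain is given as a range.

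Two stronger readings are tempting and should not be drawn:

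- A reader might infer that the plan fails because a 2-df interaction p-value shows neither direction nor time point. The T0-adjusted joint test is also a 2-df test and also rejects for harm or for an effect at one time only, so it does not cure this. Direction and timing come from the estimates at T1 and T2. The article does not say that improvement would be claimed from the omnibus p-value alone, and follow-up contrasts are detail that an article may leave to the full protocol.
- Under the unequal correlations of Step 7 with a sustained 0.6-SD effect, power is 71% for the planned test and 93% for the adjusted one. A reader might credit all 22 points to baseline adjustment. A multivariate test of the same interaction, with T0 still an outcome level, reaches 89%. So 89 − 71 = 18 points come from multivariate testing and only 93 − 89 = 4 from adjusting for T0.

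**Conclusion.** The point holds as a cheap improvement. The planned primary test spends a pre-randomisation measurement as an outcome level, and adjusting for it would usually be more efficient. For a sustained 0.6-SD effect with 20 per arm, the gain is about 14 percentage points of power at ρ = 0.5 (48% to 62%), about 7 at ρ = 0.7 (70% to 77%) and a few at ρ = 0.8. For an effect at one time under equal correlations there is essentially no difference. These figures assume complete data, and the correlation, effect size and effect pattern are assumptions because the article does not state them. The documents do not support calling the planned test invalid or the sample size of 40 wrong on this ground.

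**What to change.** Analyse T1 and T2 MAIA as the outcomes with T0 MAIA as covariate, in a mixed model with group, time, group×time, T0 and T0×time and an unstructured covariance between T1 and T2. Make the joint group effect at T1 and T2 the primary test. Report the adjusted group difference with 95% CI at each of the two times, and draw any claim of improvement from those estimates and not from the joint p-value.

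The cost is a change of analysis wording: no extra data are needed, since T0 is already collected. The downside is some loss of power if the effect appears only at T2 and the T0–T1 correlation is very high (about 52% against 60% in the case examined).

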## Methods

### Participants

Women who have experienced breast cancer in the past and that have completed cancer treatments will be included in this study. Specifically, inclusion criteria are as follows: (a) adult women (18 years and older); (b) women who have previously received a diagnosis of breast cancer (stage I and II); (c) women who have received cancer treatment (e.g., chemotherapy, radiotherapy, or monotherapy) in the past. Contrarily, exclusion criteria include people with a diagnosis of metastatic cancer and women who are unable to sign an informed consent and/or have poor knowledge of the Italian language. A sample size of at least 40 participants (please see “Data Analysis and Sample Size Estimation” section) is estimated to be involved.

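### The claim of 90% power for partial η² = 0.04 with 40 participants holds only conditionally: on the ordinary scale power is about 33%, and on the alternative scale 90% needs an unstated correlation of about 0.62 or more

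*Protocol article*

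**What the plan says.** The section on data analysis and sample size (protocol article) says the size was "calculated using G*Power 3.1.9.2 software" and names the test: "to analyze variance with repeated measure (ANOVA) with between–within interaction". The primary endpoint compares the two groups on the overall MAIA score at T0, T1 and T2.

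The stated inputs are:
- the effect: "To detect a weak-median effect size (i.e., partial η^2^ = 0.04"
- the type I error: "The type-I error rate (α) was set at 0.05 (two-sided"
- the power: "the power (1 – β) was set at 0.90"

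The result is "the required sample size is 40 (i.e., 20 participants in each group". The Participants section repeats the figure as a minimum: "A sample size of at least 40 participants". The article does not give the correlation among the three measurements (ρ), the nonsphericity correction (ε), or which effect-size definition was selected in the program.

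**The concern.** In a within-between calculation, a partial η² of 0.04 can stand for two different quantities.

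The first is the ordinary one: interaction sum of squares divided by interaction plus error sum of squares, as ANOVA output reports it. The within-subject error term already reflects ρ, so ρ does not enter the power calculation again.

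The second takes the f derived from 0.04, scales it to the total within-group standard deviation, and then divides by 1 − ρ inside the noncentrality parameter. The same 0.04 then describes a much larger effect on the ordinary scale, and the answer depends strongly on ρ.

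The article gives the one number without saying which meaning applies, and describes it in words: "To detect a weak-median effect size". This is its only power statement for the primary endpoint. A reader who takes 0.04 in the ordinary sense would treat a null interaction as good evidence against an effect of that size, believing the chance of missing it to be 10%. On that scale the chance is about 67%.

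**Working it through.** **Inputs from the article.** k = 2 groups, m = 3 times, N = 40, α = 0.05, target power 0.90, partial η² = 0.04. Calling α two-sided changes nothing, because the F test has a single rejection region.

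**Inputs not in the article, assumed and varied.** ρ, ε and the effect-size option.

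**Common steps.** f² = 0.04/0.96 = 0.04167, so f = 0.204. Degrees of freedom are df1 = (k−1)(m−1)ε and df2 = (N−k)(m−1)ε, which are 2 and 76 at ε = 1. Power comes from the noncentral F distribution with noncentrality λ.

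**1. Alternative scaling: λ = f²·N·m·ε/(1−ρ) = 5ε/(1−ρ) at N = 40**

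The plan's figure can be reproduced. With ρ = 0.63 and ε = 1, λ = 5/0.37 = 13.51, power is 0.908, and 40 is the smallest even N reaching 0.90. At ε = 1, every ρ from about 0.621 to 0.640 returns exactly 40. With ρ = 0.70 and ε = 0.75, λ = 3.75/0.30 = 12.5, power is 0.906, and N is again 40.

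The dependence on ρ is steep (N = 40, ε = 1):

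| ρ | Power |
|---|---|
| 0.3 | 0.646 |
| 0.5 | 0.799 |
| 0.6 | 0.884 |
| 0.62 | 0.900 |
| 0.65 | 0.923 |
| 0.7 | 0.957 |

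At ρ = 0.5, λ = 10 and 90% power would need N = 54. With ρ = 0.5 and ε = 0.75, power at 40 is 0.710.

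**2. Ordinary partial η²: λ = f²·(N−k)(m−1)ε**

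At ε = 1, λ = 0.04167 × 38 × 2 = 3.17 and power is 0.326. ρ does not appear in the formula. An ε below 1 only lowers power. 90% power would need N = 156. Using N in place of N−k barely changes this: power 0.341, N = 154.

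**3. What N = 40 can detect on the ordinary scale**

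At df 2 and 76, 90% power needs λ ≈ 13.17. The corresponding ordinary partial η² is λ/(λ + df2) = 13.17/(13.17 + 76) = 0.148, or about 0.15. This is nearly four times 0.04 (0.148/0.04 = 3.7).

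**4. Linking the two scales**

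Converting inputs from step 1 by the same formula:
- ρ = 0.63, ε = 1: 13.51/(13.51 + 76) = 0.151
- ρ = 0.70, ε = 0.75 (df2 = 57): 12.5/(12.5 + 57) = 0.180

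So these inputs, each of which returns 40, imply an ordinary partial η² of about 0.15 or somewhat more, not 0.04.

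**The case against.** The strongest reply is that no arithmetic error has been shown. ρ, ε and the effect-size option are free inputs that the article leaves unstated, and a condensed article may leave such settings to the full protocol. A ρ of 0.5 is an assumption about the software's default, not a figure in the document. Unremarkable pairs, such as ρ = 0.63 with ε = 1 or ρ = 0.70 with ε = 0.75, return exactly 40. Naming SPSS as a possible analysis package does not show which option was chosen in the sample-size program. And f = 0.204 lies between the usual small and medium benchmarks for f (0.10 and 0.25), so the verbal label is conventional on that scale.

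All of this stands. A reader might infer that the sample size fails to reproduce, or that true power is simply 80% or 33%. The document supports none of these without its condition. A reader might also see a missing allowance for loss to follow-up, but 40 is given as a minimum and any margin may sit in the full document. Translating f into a between-group difference in standard deviations would need an assumed pattern over time that the protocol does not state.

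The reply does not remove the ambiguity in 0.04. Supplying a high ρ rescues N = 40 only on the alternative scale, and there the detectable effect is about 0.15 or more in ordinary terms. On the ordinary scale, no ρ gives 90% power for 0.04.

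**Conclusion.** The point holds in conditional form. At two groups, three times, α = 0.05 and N = 40:

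- **Ordinary partial η².** Power for 0.04 is about 33% at ε = 1 whatever ρ is, and lower if ε is below 1. The effect detectable with 90% power is about 0.15.
- **Alternative scaling of f = 0.204.** 90% power requires ρ of at least about 0.62 at ε = 1, and more if ε is below 1 (0.70 at ε = 0.75 suffices). At an assumed ρ = 0.5 and ε = 1, power is about 80%.

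The article does not say which case applies. A stronger reading, that 40 is wrong and the trial needs 54 or 156 participants, is not supported: each figure rests on an input the article does not give. What can be said is that the statement of 90% power for a partial η² of 0.04 is not true in that measure's ordinary sense, and is true on the alternative scale only with an undisclosed correlation. These results use the noncentral F test with complete data on all 40.

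**What to change.** Keep N = 40. In the sample size section, state the effect-size option, ρ and ε that were actually entered, then make the stated property match:

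- If the ordinary definition was meant: 40 participants give 90% power for a partial η² of about 0.15, and about 33% for 0.04 (ε = 1).
- If the alternative scaling was used: give the power that the stated ρ and ε yield for f = 0.204, and add the equivalent ordinary partial η² so that it can be compared with the ANOVA output.

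The authors should not declare 80% at ρ = 0.5 unless those were their inputs. In either case, the detectable effect should not be described as weak to medium on the ordinary partial η² scale.

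The cost is a few sentences. Recruitment, procedures and analysis are unchanged. The stated sensitivity may become less favourable, and a null result would have to be read against the larger detectable effect.
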